## Abstract

**Background:**

Sleep problems are reported in up to 50% of adolescents and young adults (AYA) with cancer. Cognitive behavioural therapy for insomnia (CBTi) is considered the gold-standard treatment. In the AYA population, CBTi is associated with improvements in insomnia, daytime sleepiness, fatigue and quality of life. In adults, stepped-care interventions can improve accessibility to CBTi. This study aims to evaluate the acceptability and feasibility of a stepped-care CBTi programme in AYA with cancer.

**Methods and analysis:**

AYA (target *N* = 80) aged 16–25 with a diagnosis of cancer will be screened using the Insomnia Severity Index (ISI) and Epworth Sleepiness Scale (ESS). When sleep difficulties are identified by the ISI and/or ESS, they will be screened for obstructive sleep apnoea and restless leg syndrome and referred to a sleep service if indicated. The remainder with sleep difficulties will be offered a stepped-care sleep programme including CBT self-management and coaching (first step). Participants will then be rescreened at 5 weeks, and those with ongoing sleep difficulties will be offered individualised CBT (second step). Recruitment and retention rates, adherence to intervention and time taken to deliver screening and intervention will be collected to assess the feasibility of the programme. AYA and clinicians will complete evaluation surveys to assess the acceptability of the AYA Can-Sleep programme.

**Discussion:**

We seek to contribute to the evidence base regarding screening and treatment of sleep difficulties in the AYA population by implementing the AYA Can-Sleep programme and determining its feasibility and acceptability as an approach to care in an Adolescent & Young Adult Cancer Service.

## Background

Each year in Australia, over 1200 adolescents and young adults (AYA) aged between 15 and 25 years are diagnosed with cancer [1]. At this life stage, a cancer diagnosis comes at a critical time of growth and development with far-reaching consequences for both physical and psychosocial health [2], extending into the post-treatment survivorship phase [3, 4]. Sleep problems are among the most commonly reported consequences of cancer treatment, with up to 50% of AYA experiencing sleep disturbance and insomnia before, during and after treatment [5–7].

The most commonly reported sleep problems for AYA include problems initiating sleep, remaining asleep, excessive daytime sleepiness, fragmented sleep and excessive napping [7]. Sleep problems in AYA have been associated with emotional regulation difficulties, deficits in social skills and cognition, school and work challenges, and higher rates of depression, anxiety and posttraumatic stress disorder (PTSD) [8]. Developmentally, AYA are at increased risk biologically and behaviourally for sleep difficulties [9, 10]. Changes in circadian and hormonal processes together with external factors such as social commitments, evening technology use, high homework load or evening work lead to later bedtimes and shorter sleep duration [11, 12]. When an AYA is diagnosed with cancer, it is common for them to experience further disruptions to sleep due to factors such as frequent hospitalisations, the physical symptoms of cancer, medication and treatment side effects [6]. Following treatment, AYA are faced with many additional stressors, including ongoing physical symptoms, stress about returning to school and/or work, anxiety about a recurrence of their cancer, and ongoing medical demands [6].

Cognitive behavioural therapy (CBT) is a psychological intervention that aims to change thoughts, behaviours and emotions that can interfere or exacerbate sleep problems [13]. CBT for insomnia is delivered as a multicomponent intervention and may include sleep restriction, stimulus control, sleep hygiene, cognitive restructuring and relaxation training [14]. Whilst research has demonstrated its effectiveness in many patient populations, including adults with cancer [15], few studies have focused on its effectiveness on the AYA population. In a study with 12 AYA with cancer, Zhou et al. (2017) piloted a CBT for insomnia programme, which consisted of three individual sessions (approximately 14 days apart) with a clinical psychologist. Sleep variables were found to improve immediately post intervention (at session 3) and were sustained at 2-month follow-up [16]. In a more recent study by Zhou et al. (2020), a CBT programme called Sleep Healthy using the Internet (SHUTi) was delivered to AYA with cancer [17]. Consisting of six sessions, SHUTi is based on the fundamental strategies from CBT for insomnia and is delivered via an automated Internet programme. At the completion of SHUTi, AYA experienced improvements in several domains including daytime sleepiness, fatigue, and quality of life. These improvements were maintained up to 2 months post intervention. The SHUT-I programme however now requires a subscription (approximately US $200 per person) which may not be feasible for AYA or cancer services.

Traditional CBT is delivered through 50–60 min face-to-face sessions, with one psychologist/counsellor to one person [15]. This model is expensive and often does not fit the needs of AYA who are also juggling work, school and other social commitments. Another significant barrier in the treatment of sleep difficulties is the shortage of experts trained in CBT both in the community and in cancer centres across the world [18]. An option to improve accessibility and feasibility is self-management CBT resources. A meta-analysis of randomised controlled trials found that self-management CBT resources are an efficacious and acceptable alternative for the treatment of insomnia, especially when telephone consultation was included to encourage participation and enhance adherence [19]. Self-management CBT resources have been found to be effective in both adults with cancer [20] and AYA with cancer [17].

Whilst self-management CBT resources are an efficacious alternative, a meta-analysis indicated that sleep improvements were consistently of a lower magnitude than those from face-to-face CBT and were not a substitute for professionally administered treatment [21]. A meta-analysis of randomised controlled trials recommended the use of self-management CBT as an entry level of a stepped-care model for insomnia [19]. Stepped-care models allow for more rapid access to mental health services in a wide range of settings [22]. They are based on the premise that interventions should vary in type and intensity, especially in healthcare systems with limited resources [23]. In a stepped-care model, an entry level treatment should be the most readily accessible, cost effective, least restrictive and able to provide signficant health gain, such as self-management CBT [24]. Treatment intensity can then be stepped up if the entry level treatment is not providing significant health gain [24, 25]. With a stepped-care model to manage insomnia, the more intensive treatments (face-to-face sessions) are reserved for people who do not benefit from less intensive self-management CBT; as a result, treatment costs are reduced, and resource allocation is maximised [26].

Stepped-care interventions developed for adults with cancer have been shown to improve the accessibility to CBT for treatment of sleep difficulties [27]. There have been no published trials of stepped care for sleep difficulties in the AYA population. This study aims to evaluate the first known stepped-care programme to treat sleep difficulties in AYA with cancer.

## Methods and analysis

### Design

This study design is a prospective, single-arm study to evaluate feasibility and preliminary efficacy of an adapted stepped-care sleep intervention for AYA with sleep difficulties and cancer.

### Study setting

Outpatient cancer clinics across two specialist metropolitan hospitals in Melbourne, Australia.

### Sample size

As this is a feasibility study, a power calculation to determine sample size was not undertaken. The target sample for screening is 80 AYA with cancer across a 15-week period. This is based on expected numbers of people seen in a large tertiary cancer centre and is in line with other sleep studies in the AYA population [6, 28]. This number is also consistent with recommendations for pilot and feasibility studies [29–31] and will provide data on the acceptability and feasibility of the AYA Can-Sleep programme.

### Participants

The study includes two groups: AYA with cancer and healthcare professionals delivering cancer care to the AYA population.

### Participant inclusion criteria

#### AYA

To be eligible to participate in this study, the following criteria must be met: (i) aged between 16 and 25 years of age, (ii) have a histologically confirmed diagnosis of cancer, (iii) able to give informed consent (i.e. no psychiatric/cognitive condition that would impact informed consent, as based on clinical judgement) and (iv) able to read and write in English.

#### Healthcare professionals

To be eligible to participate in this study, healthcare professionals must be working in the outpatient cancer clinics involved in the study. These healthcare professionals may include oncologists (adult and paediatric), nurses, psychosocial oncology clinicians and allied health staff.

### Participant recruitment and consent

#### AYA

AYA will be recruited from outpatient clinics at the Peter MacCallum Cancer Centre and the Royal Women’s Hospital, Melbourne. Hospital clinic lists will be screened by the research team. AYA who meet the inclusion criteria will be approached by either a psychologist or a member of the clinical team, verbally informed of the project and invited to take part in the AYA Can-Sleep programme and its evaluation. Interested AYA will be provided with verbal and written information on the project, including study requirements and participant information and consent form (PICF). Written informed consent will be obtained in clinic by participants who agree to participate. Alternatively, for potential participants who wish to consider their involvement, an online link to the PICF will be sent via REDCap. AYA who do not return their PICF within 2 weeks of receiving it will be followed up with one phone call/voicemail and one email reminder. Those who still do not return the PICF will be considered to have declined involvement and have no further contact from the project team.

AYA who decline to participate in the study will be asked if they consent to their reasons for declining, patient information (age, sex, diagnosis, treatment received) and site they were approached at being recorded. This will allow for differences between consenters and decliners to be examined.

#### Healthcare professionals

Clinicians who have participated in the AYA Can-Sleep programme will be sent a link to the clinician engagement survey at the end of the evaluation period. Consent will be implied when clinicians return completed surveys.

### Study measures

Study measures and the timing of assessments are summarised in Table 1.

**Table 1 Tab1:** Schedule of enrolment and assessments

	Item/time	Enrolment	Rescreen	Completion
		*t*_0_	*t*_1_	*t*_2_
**Screening**				
Insomnia Severity Index	7	X	X	X
≥ 8 indicates symptomatic				
≥ 3-point change is clinically meaningful				
Epworth Sleepiness Scale	8	X	X	X
≥ 10 indicates symptomatic				
STOP-BANG	8	X		
≥ 5 are classified as high risk of moderate to severe OSA				
Restless Legs Syndrome Scale	5	X		
−5/5 at risk of restless leg syndrome				

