#### *The Epworth Sleepiness Scale (ESS)* [35]

The ESS is an 8-item self-report measure that asks participants to rate the probability of falling asleep on a scale of increasing probability from 0 to 3 for different situations that most people engage in during their daily lives including “watching TV” or “sitting and reading.” Scores of ≥ 11 will be interpreted as clinically significant, as scores from 11 to 24 represent increasing levels of excessive daytime sleepiness. The ESS has good internal consistency reliability (alpha = 0.89) and a 2-week test-retest reliability of 0.82 in both the adult and AYA populations [36].

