## Study procedures

### Initial screening and referral

Over a planned 15-week period, all participating AYA will be screened for insomnia using the ISI and ESS. Participants with scores of < 8 on ISI and score of < 11 ESS will receive no follow-up or treatment. Participants who are identified as having sleep difficulties (scores of ISI ≥ 8 and/or ESS ≥ 11) will then be asked to complete questionnaires for obstructive sleep apnoea (STOP-BANG) and restless legs syndrome (RLSS).

Participants who score high on the STOP-BANG (≥ 5) or the RLSS (i.e. yes to all questions) will be referred to the Department of Respiratory and Sleep Medicine at the Royal Melbourne Hospital, Melbourne, Australia, for further assessment. Participants who score below cutoffs on both the STOP-BANG and RLSS will be offered the AYA Can-Sleep stepped-care programme.

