### Step 1: CBT self-management resource (CBT-SM)

Participants referred to step 1 will be provided with the CBT self-management resource (CBT-SM). The CBT-SM resource includes psychoeducational material and strategies on key cognitive behavioural techniques to manage sleep difficulties. This includes the following: practical advice on how to establish good sleep hygiene habits and use relaxation techniques to promote sleep, strategies to manage common worries and cognitions that interfere with sleep and strategies to manage common cancer treatment side effects that interfere with sleep including pain and unpleasant night-time sensations including nausea, hot flushes, rash and symptoms of peripheral neuropathy.

A psychologist or member of the clinical team trained in administering the resource will provide the CBT-SM resource to the AYA and provide instructions for its use. Approximately, 3 weeks post receiving the CBT-SM resource, AYA will be contacted (via text, email or phone) by a psychologist to answer any questions the AYA might have and resolve any problems that may have arisen.

Five weeks post receiving the CBT-SM, participants will be rescreened using the ISI and ESS. For participants with scores of ISI < 8 and ESS < 11 following CBT-SM, it will be assumed that their sleep difficulties have improved, and they will receive no further treatment. If participants have ongoing sleep difficulties (i.e. scores of ≥ 8 on the ISI and/or ≥ 11 on the ESS), they will be referred for individual CBT. If the participant cannot attend individual CBT, they will be referred back to community support services and/or their GP for follow-up.

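### The Epworth cutoff is ≥ 10 in Table 1 but ≥ 11 everywhere else, so a participant with ESS = 10 and ISI < 8 is symptomatic in the table and screen-negative in the procedures

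*Protocol article*

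**What the plan says.** The protocol article gives a cutoff for the same 8-item ESS in four places.

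- **Study measures, Table 1, Screening block:** "≥ 10 indicates symptomatic".
- **The Epworth Sleepiness Scale (ESS):** "Scores of ≥ 11 will be interpreted as clinically significant, as scores from 11 to 24 represent increasing levels of excessive daytime sleepiness".
- **Initial screening and referral:** the negative rule is "Participants with scores of < 8 on ISI and score of < 11 ESS will receive no follow-up or treatment". The positive rule, which leads to the STOP-BANG and restless legs questionnaires and then to the offer of Step 1, is "scores of ISI ≥ 8 and/or ESS ≥ 11".
- **Step 1: CBT self-management resource:** at the 5-week rescreen, the rule for no further treatment begins "For participants with scores of ISI < 8 and ESS < 11 following CBT-SM". Referral to individual CBT requires "scores of ≥ 8 on the ISI and/or ≥ 11 on the ESS".

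After individual CBT (section Individual CBT), the decision uses ISI ≥ 8 alone.

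**The concern.** The ESS cutoff is a decision threshold. With the ISI, it determines who counts as having sleep difficulties at entry, who goes on to the sleep apnoea and restless legs screen, who is offered Step 1, and who is stepped up at 5 weeks. Two values for it cannot both be applied.

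Nothing in the article explains the difference. It is one scale throughout, and no section makes a score of 10 a separate or borderline category. The ISI (≥ 8), STOP-BANG (≥ 5) and restless legs (5 of 5) cutoffs in the same block of Table 1 match the text, so a reader has reason to trust the ESS line as well.

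The study reports the quantities that depend on this threshold. The Discussion lists prevalence of sleep difficulties among the things the study is designed to assess. Operational data lists referral rates and uptake of follow-up care as feasibility measures. Their numerators or denominators depend on who is screen-positive.

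**Working it through.** **1. Where the two cutoffs disagree**

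Rule A (Table 1 cutoff): positive if ISI ≥ 8 or ESS ≥ 10. 
Rule B (procedures): positive if ISI ≥ 8 or ESS ≥ 11.

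| ESS | ISI | Rule A | Rule B |
|---|---|---|---|
| ≤ 9 | 0–7 | negative | negative |
| 10 | 0–7 | **positive** | **negative** |
| ≥ 11 | 0–7 | positive | positive |
| any | ≥ 8 | positive | positive |

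The ISI runs from 0 to 28 and the ESS from 0 to 24, which gives 29 × 25 = 725 possible score pairs. The rules differ in 1 × 8 = 8 of them: ESS = 10 with ISI 0 to 7. This count locates the conflict. It is not a probability, because the pairs are not equally likely.

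**2. What happens to a participant in that cell**

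- At entry: symptomatic by Table 1. Under Initial screening and referral there is no follow-up or treatment, and so no STOP-BANG or restless legs screen and no offer of Step 1.
- At the 5-week rescreen: symptomatic by Table 1. Under the Step 1 section, assumed improved and not referred to individual CBT.
- After individual CBT: the decision is unaffected, because only the ISI is used. Table 1 also schedules the ESS at this visit, so a count of ESS-symptomatic participants there would still be ambiguous.

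**3. How many participants could be at exactly 10**

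The article gives no mean, SD or distribution for the ESS, so the size cannot be derived from it. As an assumption, take a normal approximation with mean m from 7 to 9 and SD s from 4 to 5:

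P(ESS = 10) ≈ Φ((10.5 − m)/s) − Φ((9.5 − m)/s)

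| m | s | Calculation | P | × 80 |
|---|---|---|---|---|
| 7 | 5 | Φ(0.700) − Φ(0.500) = 0.7580 − 0.6915 | 6.7% | 5.3 |
| 7 | 4 | Φ(0.875) − Φ(0.625) = 0.8092 − 0.7340 | 7.5% | 6.0 |
| 8 | 4.5 | Φ(0.556) − Φ(0.333) = 0.7107 − 0.6306 | 8.0% | 6.4 |
| 9 | 5 | Φ(0.300) − Φ(0.100) = 0.6179 − 0.5398 | 7.8% | 6.2 |
| 9 | 4 | Φ(0.375) − Φ(0.125) = 0.6462 − 0.5497 | 9.6% | 7.7 |

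The extremes of the grid are the first and last rows: about 6.7% to 9.6%, or 5 to 8 of the 80 targeted for screening. (Using the density at 10 instead of the interval gives 9.7% in the last row, with the same whole-number range.)

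**4. How many of those change status**

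Only those who also have ISI below 8. The article does not give the joint distribution of the two scales, so this fraction could lie anywhere between none and all. On these assumptions, between 0 and about 8 of 80 change status at entry. The screen-positive proportion then moves by at most 7.7/80, about 9.6 percentage points. At the rescreen the base is the participants who took up Step 1, whose number the article does not give, so no figure is offered there.

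**The case against.** The strongest reply is that the working procedure is clear. Table 1 is a summary schedule and its ESS line labels a score without assigning any action. Every sentence that assigns an action, both negative and positive rules at entry and at rescreen, uses 11. Staff who follow the procedures would act consistently, and the correction is one of wording. This stands as far as it goes: Table 1 is the outlier. It does not settle the matter, because the article nowhere says which value is intended, and the table labels as symptomatic a person whom the procedures send away without follow-up.

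A reader might infer more than the article supports:

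- *Anyone scoring 10 goes untreated.* No. With ISI ≥ 8 the participant is positive under either cutoff.
- *The two hospitals are applying different cutoffs, or the electronic scoring is set wrongly.* The article documents neither. REDCap is described for sending consent forms, managing data and keeping withdrawal records, and no scoring or branching rule is given.
- *The feasibility and efficacy criteria are compromised.* The consent proportion is determined before any ESS score is taken. The clinically meaningful change in Data analysis is 3 or more points on the ISI. The ESS cutoff can alter who enters that count, but not how it is defined.
- *The number affected is known.* It is not. Any single figure, including one that halves the group for ISI positivity, would rest on inputs the article does not contain.

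**Conclusion.** The contradiction is real, and it concerns a threshold that governs entry to further screening and Step 1 and the 5-week step-up. That makes it more than a typographical matter, although its reach is narrow: it is confined to ESS = 10 with ISI below 8. It affects the screen-positive proportion, the numbers offered Step 1 and stepped up, and the uptake denominators. It leaves the consent criterion, the ISI change criterion and the decision after individual CBT unchanged. The logical conflict rests on the text alone. The size, at most about 8 of 80 at entry and possibly none, rests on the assumed normal approximation and on an unknown ISI split. The documents do not say which cutoff is intended, and no view is taken here on which is right.

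**What to change.** The sponsor should reconcile the four places to one ESS cutoff and state it identically in Table 1, the ESS description, Initial screening and referral, and the Step 1 section. Fig. 1, which is not shown in the text reviewed, should be checked for agreement.

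If screening has begun, the sponsor should also confirm which cutoff was actually applied and report how many participants had ESS = 10 with ISI below 8, at entry and at the 5-week rescreen. Readers can then see how far the screen-positive proportion and the step counts depend on the choice.

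The cost is a wording correction and, if data exist, one check of practice and one tabulation of scores already collected. No new data and no change to the design are needed.

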**Feasibility**				
Proportion of people approached who consent	-	X	X	X
> 50% indicates programme is feasible				
Dropout rate	-	X	X	X
> 40% indicates programme is feasible				
**Acceptability** — *quantitative and qualitative data*				
Participant experiences survey — screening questionnaires	5	X		
Participant experiences survey — post follow-up care	10		X	X
Clinician engagement survey	14			X
Other variables				
Demographic and cancer information	4	X		
Administrative and fidelity data		X	X	X

X, measure administered at that time point

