### Operational data

Clinician time taken to deliver screening and intervention will be collected on a project-specific case report form. Referral rates, participant uptake of follow-up care, number of weeks completed of intervention received, uptake of evaluation participation of both AYAs and clinicians and those that refuse the intervention despite meeting eligibility criteria (including reasons for declining participation) will also be collected to assess feasibility of the program.

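### The two feasibility criteria in Table 1 can be met when few symptomatic AYA start or finish the programme: consent precedes sleep screening, dropout has no denominator and a reversed threshold, and uptake has no criterion

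*Protocol article*

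**What the plan says.** The Feasibility block of Table 1 holds the only two feasibility measures with a threshold. One is "Proportion of people approached who consent", with the rule "> 50% indicates programme is feasible". The other is dropout rate, with the rule "> 40% indicates programme is feasible". Both rows are marked at t0, t1 and t2. No denominator or definition of a dropout is given.

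Under Participant inclusion criteria, entry depends on age, a cancer diagnosis, capacity to consent and English, not on a sleep problem. Under Initial screening and referral, those below both the ISI and ESS cutoffs "will receive no follow-up or treatment". Those above a cutoff are offered Step 1 unless STOP-BANG or the RLSS sends them to the sleep service.

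Operational data lists "participant uptake of follow-up care", weeks of intervention completed and refusals by eligible AYA as data for judging feasibility, with no threshold for any of them. Sample size states: "The target sample for screening is 80 AYA with cancer across a 15-week period". It adds that "a power calculation to determine sample size was not undertaken".

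**The concern.** What is to be judged feasible is a stepped treatment programme. The useful questions are whether symptomatic AYA take up each step when it is offered, and whether those who start stay to the next assessment. Consent cannot answer the first, because it is given before anyone knows whether treatment will be offered. Dropout could answer the second, but only with a denominator limited to people who can drop out and a threshold pointing the right way. AYA who screen negative finish at t0, so including them lowers the rate however the programme performs. In a single-arm study meant to inform a standard approach to care, a formal verdict of feasible could then stand beside poor uptake and poor completion.

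**Working it through.** **Plan's own figure.** The 80 comes from expected clinic numbers, similar studies and pilot-study guidance. There is no formula to reproduce.

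**Order of events.** Eligibility (no sleep criterion) → approach → consent → ISI and ESS → STOP-BANG and RLSS if positive → offer of Step 1 → rescreen at 5 weeks (t1) → offer of Step 2 if still positive → rescreen after session 4 (t2). Consent comes before every step that reveals who needs treatment.

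**Dropout over all enrolled, read as an upper limit of 40%.** Allowed dropouts = 0.40 × 80 = 32. Only symptomatic AYA can leave treatment, so the share of them that may be lost is 32 / (80 × s), where s is the symptomatic share. The Background cites up to 50% from the literature. This study's own screen-positive rate is not given, so s is varied as an assumption:

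| s | symptomatic | share that may be lost |
|---|---|---|
| 30% | 24 | all (32 exceeds 24) |
| 40% | 32 | 32/32 = 100% |
| 50% | 40 | 32/40 = 80% |
| 60% | 48 | 32/48 = 67% |

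**Dropout over starters.** With 40 starters the limit allows 0.40 × 40 = 16 losses, so it does restrain non-completion. It places no bound on how many start.

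**Illustration (invented counts, not a forecast).** 160 approached, 81 consent: 81/160 = 50.6%, which passes. Of these, 40 are positive and offered Step 1, 15 start and 8 stop.
- Uptake: 15/40 = 37.5%, tested by no rule.
- Dropout over all enrolled: 8/81 = 9.9%. Dropout over starters: 8/15 = 53.3%.
- With an upper limit of 40%, the first passes and the second fails. With the rule as printed (above 40%), the first fails and the second passes.
- If only 6 of the 15 stop, 6/15 = 40% sits at the limit even among starters, yet only 9 of 40 offered (22.5%) finish.

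**Printed direction.** Taken literally, more than 32 dropouts of 80, or more than 16 of 40, would count in favour of feasibility.

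**Numbers entering each step.** Offered Step 1 = 80 × s × (1 − r), where r is the share referred to the sleep service (not given; 0 to 20% assumed). At s = 50% this is 40 down to 32; at s = 30%, 24 down to 19. If 40 start and half remain symptomatic (assumed), Step 2 has about 20.

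**Precision at 40% dropout.** Exact (Clopper-Pearson) 95% limits, with x dropouts among n starters: lower = 2.5% quantile of Beta(x, n − x + 1); upper = 97.5% quantile of Beta(x + 1, n − x).
- 16/40: 24.9% to 56.7%
- 12/30: 22.7% to 59.4%
- 8/20: 19.1% to 63.9%

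**The case against.** Several stronger readings are tempting, and the article does not support them.

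- A reader might infer that both criteria belong to the screening stage. Table 1 marks dropout at t1 and t2 as well, so it can bear on finishing. Its faults are the missing denominator and the reversed sign.
- A reader might infer that the plan counts dropout over all enrolled. It does not say so; the dilution is conditional on that choice.
- A reader might infer that Sample size passes 80 off as the number treated. It calls 80 a screening target and openly declares that no power calculation was done, which is acceptable for a feasibility study. Screening is itself under evaluation, so 80 is a relevant number.
- A ceiling of 40 in Step 1 is not established. The literature figure concerns sleep disturbance and insomnia, not positivity on ISI ≥ 8 and/or ESS ≥ 11.

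Beyond these, AYA are invited to the programme as well as its evaluation, so consent carries some information about interest in it. Uptake, weeks completed and refusals will be collected and described, so poor uptake would be visible in the report. A condensed article may also leave a denominator to the full protocol.

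All of this narrows the point without removing it. The article chose to publish decision rules for feasibility. As printed, one has the wrong direction, and neither responds to uptake under any choice of denominator. Visible data do not change what the stated rules conclude.

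**Conclusion.** The point holds in limited form. Consent measures willingness to enrol and be screened. Dropout is undefined as to denominator and printed in reverse. Uptake at either step has no criterion. The stated rules can therefore return feasible when few eligible AYA start or finish.

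The size depends on the denominator. Over all 80, with 40 symptomatic, a 40% upper limit tolerates the loss of 80% of the symptomatic group; over 40 starters it tolerates 16 losses but leaves uptake unconstrained. This rests on two assumptions: that the printed threshold is meant as an upper limit, and that about half screen positive. The dilution is weaker if more do and stronger if fewer do. The reversed sign, the missing denominator and the absence of an uptake criterion need neither assumption. This should be changed before the feasibility results are judged.

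**What to change.** In Table 1:

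1. Define dropout separately for each step, among AYA who start it. Step 1: given the CBT-SM resource but without a t1 rescreen, over all given the resource. Step 2: attended session 1 but did not complete the sessions, over all who attended session 1. Exclude screen-negatives and those referred to the sleep service.
2. Correct the direction, either as an upper limit on dropout or by restating the row as retention. The sponsor must say which was meant, because the two differ: retention above 40% would tolerate almost 60% loss, whereas a 40% limit on dropout requires at least 60% retention.
3. Add uptake (started / offered) at each step as a feasibility criterion, at a level the sponsor fixes in advance. The 50% already used for consent is one possibility, not a recommendation derived from data.
4. Report each proportion with an exact 95% interval.

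In Sample size, add the number expected to enter each step: about 40 or fewer of 80 at Step 1 if the cited figure applies to this study's screening rule, labelled as an assumption.

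The cost is wording and analysis. Uptake, weeks completed and refusals are already listed under Operational data; the sponsor should confirm that attendance at each Step 2 session is recorded. The downside is one more criterion to meet and visibly wide intervals.

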## Discussion

This study aims to evaluate the first known stepped-care programme to treat sleep difficulties in AYA with cancer. This study protocol is designed to assess valuable information regarding recruitment, prevalence and severity of sleep difficulties in the AYA population, retention and completion rates and the acceptability of a stepped-care programme to treat sleep difficulties to AYA and clinicians. These findings will help to assess the feasibility and acceptability of stepped-care CBTi as a standard approach to care in an Adolescent & Young Adult Cancer Service.

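### The dropout criterion in Table 1 is reversed or mislabelled: as printed, dropout above 40% counts as evidence that the programme is feasible

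*Protocol article*

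**What the plan says.** Table 1 (Study measures) attaches a numeric threshold to two feasibility measures. For the proportion of approached people who consent, the rule is "> 50% indicates programme is feasible". For the dropout rate, it is "> 40% indicates programme is feasible".

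Elsewhere the article names the complementary measure and gives no threshold. The abstract, under Methods and analysis, lists "Recruitment and retention rates, adherence to intervention" among the data used to assess feasibility. The Discussion refers to "retention and completion rates". The sections on operational data and data analysis give no cutoff for dropout or retention. Under Sample size, the screening target is 80, and the article states that "a power calculation to determine sample size was not undertaken".

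**The concern.** Consent is better when higher and dropout is better when lower, yet both rows use the same greater-than sign. Read literally, the second row rewards losing participants: a programme that more than half of them leave satisfies it, and one that keeps nine in ten does not.

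Feasibility is the stated aim and no hypothesis test stands behind the conclusion, so these two thresholds are the only numeric standards the article sets for it. A reader can see that the dropout line is wrong but cannot tell what was meant. If the choice between repairs is made once the dropout rate is known, the success criterion will have been chosen after the result.

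**Working it through.** The article derives no sample size or power from this threshold, so there is no published figure to reproduce. The check is of the rule's direction and of how far the possible repairs differ.

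**Inputs.** The 40% threshold comes from Table 1 and the screening target of 80 from Sample size. The article gives no denominator for dropout, so n = 20, 40 and 80 are assumptions; 80 is the screening target.

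**1. The rule as printed.** Feasible means observed dropout above 40%. With n participants that is at least r = floor(0.4n) + 1 dropouts:

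- n = 20: 0.4 × 20 = 8, so r = 9
- n = 40: 0.4 × 40 = 16, so r = 17
- n = 80: 0.4 × 80 = 32, so r = 33

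With n = 40, therefore, 17 to 40 dropouts meet the criterion and 0 to 16 do not.

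If the true dropout probability is p and X is binomial(n, p), the chance of meeting the criterion is P(X ≥ r):

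| n | p = 20% | p = 40% | p = 60% | p = 80% |
|---|---|---|---|---|
| 20 | 0.010 | 0.404 | 0.944 | >0.999 |
| 40 | 0.001 | 0.432 | 0.992 | >0.999 |
| 80 | <0.001 | 0.452 | >0.999 | >0.999 |

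The chance of passing rises with dropout at every n. The inversion does not depend on the assumed denominator.

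**2. The two repairs.**

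- *Sign wrong:* dropout < 40%, which is retention > 100% − 40% = 60%. With n = 40, at most 15 dropouts.
- *Label wrong:* retention > 40%, which is dropout < 100% − 40% = 60%. With n = 40, at most 23 dropouts.

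The bars are 60% − 40% = 20 percentage points apart. Observed dropout from 40% to just under 60% (16 to 23 of 40) fails the first and passes the second.

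Chance of being called feasible, n = 40:

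| True dropout | As printed | Dropout < 40% | Retention > 40% |
|---|---|---|---|
| 20% | 0.001 | 0.997 | >0.999 |
| 40% | 0.432 | 0.440 | 0.992 |
| 50% | 0.866 | 0.077 | 0.866 |
| 60% | 0.992 | 0.003 | 0.432 |

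Both repairs run in the sensible direction, but they are different rules. At 50% true dropout they give 0.077 and 0.866.

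**3. Can the text settle which was meant?** The abstract and Discussion speak of retention, which fits a mislabelled row. The row itself says dropout, which fits a reversed sign. No other section carries a threshold, so the article does not decide between them.

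**The case against.** The strongest reply is that this is an obvious slip with little practical consequence. Feasibility data are to be analysed descriptively. The article ties no go/no-go decision, stopping rule or sample size to the 40%, and no analyst is likely to report high dropout as success. The table also prints a stray-looking minus sign in its restless legs row, so a typesetting error is conceivable. Finally, the table says only what indicates feasibility and states no failure rule, and the 40 participants are not a figure from the article.

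Some of this stands. The sample size is unaffected. That low dropout would fail is an inference: strictly, it does not meet the printed criterion. The counts out of 40 are illustrative. An analyst would probably notice the reversal, so the more realistic harm is an undefined threshold.

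The rest does not rescue the line. A descriptive analysis still uses the threshold to label the programme feasible. The greater-than sign is clean and matches the consent row above, where it is correct, and a typesetting cause would not remove the need to correct the text. Recognising a slip does not tell the reader which of two materially different rules replaces it. The percentage-point argument holds at any n.

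**Conclusion.** The concern holds. One of the two numeric feasibility criteria is wrong as printed and is corrected nowhere else in the article. Its direction is reversed at every sample size tried, and the plausible repairs lie 20 percentage points apart, with opposite conclusions for observed dropout from 40% to just under 60%. The reversal and the gap between repairs follow from the printed rule alone. Only the probabilities and the counts rest on an assumed denominator (20, 40 or 80) and independent dropout at a common rate. The article does not show which repair was intended. Because feasibility is the study's aim, the rule must be fixed before the data are analysed.

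**What to change.** The sponsor should confirm the intended rule against the ethics-approved protocol and correct the Table 1 row to one of these:

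- dropout rate < 40% (equivalently, retention > 60%) indicates feasibility; or
- retention rate > 40% (equivalently, dropout < 60%) indicates feasibility, with the row renamed.

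The article supports neither as a default. It would help to state in the same edit from which point dropout is counted (consent, positive screen or start of step 1). The correction should be dated before the analysis and published, and the registry entry updated if it carries the same text.

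The cost is a one-line change to the table, with no extra data or participants and no effect on the screening target of 80.
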